### Blinding and study group allocation

2.10

Subjects will be divided into AT or NT group according to whether they had a history of receiving systemic antidepressant treatment in early stage. The screening process will be finished by two senior psychiatrists, and then the following rating works will be handed over to other investigators, which could keep the latter investigators blind to the subjects’ group assignments.

### Study procedures

2.11

Subjects will not be engaged with any interventions in this study. Two senior psychiatrists are in attendance of screening the patients along the inclusion/exclusion criteria, and then all patients who meet both criteria and are willing to participate in this study will sign the informed consent before enrollment. Especially, all patients will be screened with Hypomania Check List‐32 items (HCL‐32) to detect the potential hypomanic symptoms in early stage. The participants will be divided into AT or NT group according to their history of systemic antidepressant treatment in early stage, which is done by the two senior psychiatrists. Then the senior psychiatrists will also collect additional study parameters, including age, sex, nation, age of onset, and score of Premorbid Adjustment Scale (PAS). Furthermore, the information about history of treatments and diagnosis will be further confirmed with medical documentary and patients’ guardians. Afterward, other investigators will finish the rating work of the remaining scales. The whole procedure should be done within 180 min. Finally, 10 ml of venous blood is adopted for measuring NSE (see Figure 1).

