### Statistical analysis

2.19

The data obtained from questionnaires and basic information are expressed in “mean ± standard deviation” in the case of normal distributions and in median and quartile in the case of nonnormal distributions. The comparisons in scores of each scale between two groups will be made by Covariance Analysis; the Chi Square and Analysis of Variance (ANOVA) test will be used to test the consistency of match between groups for factors such as age, sex, MADRS scores, YMRS scores, PAS scores, use of mood stabilizers, age of onset, number of attacks, and so forth, and the factors with significantly different distributions between two groups will be used as covariates. Furthermore, the two groups of patients will be combined as a whole and then Multiple Linear Regression equations will be used to analyze the linear relationship between each factor and neurocognitive function. The test level is α = 0.05.

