
To increase the power of this study, we have some considerations as following. First, we will perform the PAS measurement to adjust the potential difference in premorbid function that may confound the cognitive performance of participants. Second, it is required that participants should have a euthymic state for 4 weeks at least before enrollment because the duration in euthymia is associated with the quality of life (Pascual‐Sánchez et al., 2019), which has been found associated to cognitive function (Sánchez‐Morla et al., 2009). Third, we have two separate groups of investigators before and after group assignment to keep the later investigators blind to the assignment and then to avoid subjective bias on assessment of scales. Lastly, we set the range of age between 18 and 50 years to decrease the influence of aging in cognitive performance.

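### The Premorbid Adjustment Scale, a candidate covariate meant to handle premorbid confounding, is scored after group assignment by the psychiatrists who made the assignment, outside the blinding the protocol describes

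*Protocol article*

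**What the plan says.** Section 2.11 (Study procedures) sets out an order of work. The senior psychiatrists screen. Participants are then placed in AT or NT "according to their history of systemic antidepressant treatment in early stage, which is done by the two senior psychiatrists". The next step is: "Then the senior psychiatrists will also collect additional study parameters, including age, sex, nation, age of onset, and score of Premorbid Adjustment Scale (PAS"). Only after that do we read that "other investigators will finish the rating work of the remaining scales".

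Section 2.10 (Blinding and study group allocation) describes the safeguard: screening is done by the two psychiatrists, and "then the following rating works will be handed over to other investigators, which could keep the latter investigators blind" to group. The Discussion repeats it as a strength of the design: "we have two separate groups of investigators before and after group assignment to keep the later investigators blind to the assignment", with the stated purpose of avoiding subjective bias in the scales.

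Two further places fix what PAS is for. The Discussion puts it first among the design considerations: "First, we will perform the PAS measurement to adjust the potential difference in premorbid function that may confound the cognitive performance of participants". Section 2.19 (Statistical analysis) lists PAS scores among the factors tested for balance between groups and says that "the factors with significantly different distributions between two groups will be used as covariates". Section 2.12 describes PAS as a retrospective instrument.

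**The concern.** PAS is scored after assignment by the people who made the assignment. It is the one scale that section 2.11 places between the grouping step and the handover, so the separation of raters does not cover it. The raters know the exposure. The Background also states an expectation that early antidepressant treatment harms cognition, social function and quality of life.

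A retrospective rating made with exposure known can drift between groups. If it did, the covariate meant to remove premorbid confounding would carry a group difference of its own. Under section 2.19 that could act twice. It could make PAS differ significantly and so bring it into the covariance analysis, and once there it would move the adjusted AT-NT difference in cognition.

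**Working it through.** **Step 1: who knows what, and when.**

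| Step in section 2.11 | Done by | Group known? |
|---|---|---|
| Screening | two senior psychiatrists | being established |
| Division into AT or NT | two senior psychiatrists | yes |
| PAS and other additional parameters | two senior psychiatrists | yes |
| Remaining scales | other investigators | no, by design |

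Section 2.10 and the Discussion describe a handover at assignment, but section 2.11 places the handover after PAS. The statements do not match for this one scale. This part needs no arithmetic.

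**Step 2: what a rating shift would do.** The protocol gives no figure for this, so there is nothing to reproduce and what follows is an illustration.
- From the protocol: 62 per group and test level 0.05 (sections 2.6 and 2.19), two-sided (section 2.6).
- Assumed: no true group difference in premorbid adjustment or cognition; both in SD units; PAS-cognition correlation r of 0.3 or 0.5 in absolute value; a rating shift b in the AT group of 0.2, 0.3 or 0.5 SD.

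*Chance that PAS is selected.* The standard error of the PAS difference is √(2/62) = 0.180. The probability of p < 0.05 is Φ(b/0.180 − 1.96) + Φ(−b/0.180 − 1.96). With b/0.180 = 1.11, 1.67 and 2.78, this gives 0.200, 0.386 and 0.795. With no shift it is 0.05.

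*Bias if PAS were always adjusted for.* This is r × b: 0.3 × 0.2 = 0.06 and 0.5 × 0.2 = 0.10; 0.3 × 0.5 = 0.15 and 0.5 × 0.5 = 0.25.

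*Average bias under the section 2.19 rule.* A simulation of 4,000 trials per setting adjusted for PAS only when it differed at p < 0.05 and otherwise compared the groups without adjustment.

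| Shift b | PAS selected (simulated) | Average bias, r = 0.3 / 0.5 | False positives, r = 0.3 / 0.5 |
|---|---|---|---|
| 0 | 4.5% / 4.9% | −0.001 / −0.001 | 5.2% / 4.8% |
| 0.2 | 19.3% / 19.6% | 0.028 / 0.045 | 5.1% / 5.3% |
| 0.3 | 37.7% / 38.8% | 0.054 / 0.090 | 5.9% / 8.4% |
| 0.5 | 77.8% / 79.7% | 0.137 / 0.225 | 12.8% / 28.4% |

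A closed form checks the bias column. The average bias is r × {b·P + 0.180 × [φ(1.96 − b/0.180) − φ(1.96 + b/0.180)]}, where P is the selection probability above.
- b = 0.2: 0.2 × 0.200 + 0.180 × (0.279 − 0.004) = 0.089. Multiplied by 0.3 and 0.5, this is 0.027 and 0.045.
- b = 0.5: 0.5 × 0.795 + 0.180 × 0.284 = 0.449. Multiplied by 0.3 and 0.5, this is 0.135 and 0.224.

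These agree with the simulation to within its error.

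**Step 3: direction.** If AT patients are rated spuriously worse before illness, adjustment credits part of their poorer cognition to premorbid status and hides harm. If they are rated spuriously better, adjustment exaggerates harm.

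**The case against.** The strongest reply is that the protocol claims blinding only for the later investigators, and that claim is kept: every outcome scale is rated by people not told the group. This stands. The point concerns one covariate, listed in section 2.19 beside age, sex, MADRS, YMRS, mood stabilizer use, age of onset and number of attacks, and it does not touch the outcome ratings.

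It is also fair that the expectation of harm concerns function after treatment, not before illness. The document gives no reason why PAS should move, or which way. Serious inflation of false positives in the illustration needs a shift of half a standard deviation, for which the document offers no evidence. This stands too, and it limits what may be claimed.

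A third reply is that the psychiatrists must know treatment history in order to assign groups. That is true, but nothing requires the same people to score PAS afterwards.

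A reader might go further in two ways, and the document supports neither.
- One might infer that any shift goes in full into the adjusted difference. Under section 2.19 PAS enters only when it differs significantly, so at a 0.2 SD shift the average bias is 0.03 to 0.05 SD, not 0.06 to 0.10.
- One might divide 0.06 to 0.25 SD by the planned δ of 0.3 and report 20 to 83% of the target effect. Section 2.6 divides δ by a separate S that it does not state, so δ = 0.3 is 0.3 SD only if S = 1. That would need 2 × [(1.96 + 0.84)/0.3]² ≈ 175 per group. For 62 per group, S is about 0.3 × √31 / 2.80 = 0.60, a target of about 0.5 SD, against which 0.06 to 0.25 SD is about 12 to 50%. Because S is not given, no percentage of δ should be quoted.

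**Conclusion.** The procedural point holds on the text alone. PAS is scored after assignment, by the assigning psychiatrists, with exposure known, and the protocol's two descriptions of its blinding do not fit that. It matters because the Discussion names PAS as the means of adjusting for premorbid confounding, and because the section 2.19 rule lets a rating difference decide whether PAS is used at all.

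The document shows exposure to bias, not bias. The size depends on the assumed shift and correlation: negligible to small at 0.2 SD (error rate still near 5%), modest at 0.3 SD (6 to 8%), and material at 0.5 SD. The direction is unknown. This is worth correcting because the correction is cheap. It is not a threat to the blinding of the primary endpoints.

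**What to change.** In sections 2.10 and 2.11, assign PAS to the blinded investigators in the same session. Have it rated after the cognitive and other outcome scales, and ask participants not to mention past treatment. The order matters: a history scale may prompt a patient to disclose earlier antidepressant use, and if PAS comes last this cannot unblind the outcome ratings. Then align section 2.10, section 2.11 and the Discussion so that all three say the same about who rates what after assignment.

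Leaving PAS with the psychiatrists but completing it before any treatment history is taken is less workable, because the exclusion criteria they screen for already call for treatment information (recent electroconvulsive therapy and recent drug use).

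The cost is a slightly longer blinded session, within the 180 minutes allowed for the whole procedure, with no extra staff or visit. A small risk of disclosure during PAS itself remains.

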**FIGURE 1 brb32360-fig-0001:**
[figure not shown]
Study flowchart AT, systemic antidepressant treatment; GAF, Global Assessment Function; NSE, neuron‐specific enolase; NT, no systemic antidepressant treatment; PANAS, Positive and Negative Affect Scale; PAS, premorbid adjustment scale; PSQI, Pittsburgh Sleep Quality Index; WHOQOL‐BRIEF, Methods Checklist on Quality of Life issued by World Health Organization‐Brief version.

### Scale assessments

2.12

COBRA will be used to assess subjective cognitive function, including verbal learning and memory, working memory, processing speed, executive functions, attention/concentration, and mental tracking. The summed scores of each item yield a total COBRA score, which is negatively correlated with subjective cognitive impairments.

SCWT, CVFT, and TMT‐B will be used to assess executive function, with higher scores indicating worse cognitive functioning.

DSFB, DSC of WAIS‐RC, and TMT‐A will be used to assess attention and processing speed. Higher scores for TMT‐A represent worse cognitive performance, and higher scores for DSFB and DSC of WAIS‐RS indicate better cognitive functioning.

VRP and VRC of WMS‐R will be used to assess visual memory, with higher scores indicating better cognitive functioning.

C‐AVLT will be used to measure verbal learning and memory domain. The higher number of word recall is associated with better verbal memory.

WHOQOL‐BRIEF will be used to assess the quality of life for the last 2 weeks prior to the assessment. It measures perceived quality of life for the domains of psychological health, physical health, social relationships, and environment as well as satisfaction with general health.

PSQI will be used to evaluate the quality of sleep for the last month, with a summed score ranging from 0 to 21, and a higher score indicates a worse sleeping quality.

PANAS will be used to detect the change in positive and negative affect. It is a self‐report instrument measuring the affective component of subjective well‐being, in which a higher score for each item refers to a higher degree for positive or negative affect.

MADRS will be used to assess the severity of depressive symptoms. The scale score ranges from 0 to 60, with a cutoff of 12 for depressive state.

YMRS will be used to assess the severity of manic symptoms. It includes 11 items, with a score not less than 6 indicating a manic state.

PAS will be used to evaluate the premorbid adjustment ability (Shi et al., 2013). PAS was designed for quantifying premorbid status in patients with schizophrenia originally, and now it has also been used in other field such as the study of mood disorders, coming to be regarded as a gold standard of retrospective assessment instrument.

MINI will be used to diagnose the initial episode of depressive disorder retrospectively.

HCL‐32 will be used to detect the potential hypomanic symptoms in early stage. It contains 32 items with “yes” and “no” options. When 14 items out of 32 items are “yes,” it indicates a hypomanic or manic state.

GAF will be used to assess patients’ functions psychologically, socially, and professionally. It is rated on a scale of nine levels, with higher level referring to better functions.

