
The current study attempts to clarify this question by making comparisons in neurocognitive function between bipolar patients who had a depressive episode as initial onset and being with and without systemic antidepressant treatment (received adequate dosage of antidepressants for 6 weeks at least) in early stage. Furthermore, the social functions and quality of life will also be investigated because both items are highly associated with cognitive functions and are indicative for functional rehabilitation. Apart from those, we will also study the influence of antidepressants used in early stage on impulsiveness, quality of sleep, and positive and negative affect. Lastly, peripheral neuron‐specific enolase (NSE) will be evaluated. NSE, a cell‐specific isoenzyme of glycolytic enolase, is known as a sensitive marker of neuronal damage (Isgrò et al., 2015). It has been showed that high level of serum NSE was related to mild cognitive dysfunction in patients with diabetic retinopathy (Yu et al., 2020) and that serum NSE levels of BD patients were significantly different from healthy controls (Akcan et al., 2018). In this regard, it is expected to examine the potential association between serum NSE level and cognitive function of BD patients. Finally, although it is mainly an explorative investigation and is informative for clinical practice regardless of outcomes, we expect that systemic antidepressant treatments in early stage could negatively affect the neurocognitive function, social functions, and quality of life of patients with BD.

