### Study endpoint

2.7

Main study endpoints include neurocognitive functioning, which can be assessed by:
Subjective cognitive measures: The Cognitive Complaints in Bipolar Disorder Rating Assessment (COBRA) (Rosa et al., 2013).Objective cognitive measures: The Stroop Color and Word Test (SCWT) (Golden, 1978), the categorical verbal fluency test (CVFT) (animal naming) (Chen et al., 2000), Chinese Auditory Verbal Learning Test (C‐AVLT) (Lee et al., 2002), and the Trail Making Test Part B (TMT‐B) (Lu & Bigler, 2000); the Digital Span Forward and Backward subtest (DSFB) and the Digit Symbol Coding subtest (DSC) of the Wechsler Adult Intelligence Scale‐Revised by China (WAIS‐RC) (Gong, 1982) and Trail Making Test Part A (TMT‐A) (Lezak et al., 2004); and the Visual Reproduction subtest (VRP) and the Visual Recognition subtest (VRC) of the Wechsler Memory Scale‐Revised (WMS‐R) (Gong, 1987).

Secondary study endpoints are as follows: Global Assessment Function (GAF), Methods Checklist on Quality of Life issued by World Health Organization‐Brief version (WHOQOL‐BRIEF), Pittsburgh Sleep Quality Index (PSQI), Positive and Negative Affect Scale (PANAS), and neuron‐specific enolase (NSE).

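### The article states the scoring direction of verbal fluency (CVFT, animal naming) the wrong way round, and probably that of COBRA too, so a difference on these main endpoints would be misread.

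*Protocol article*

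**What the plan says.** Section 2.7 (Study endpoint) makes neurocognitive functioning the main endpoint and lists the measures. The subjective one is given as "Subjective cognitive measures: The Cognitive Complaints in Bipolar Disorder Rating Assessment (COBRA". The objective ones include "the categorical verbal fluency test (CVFT) (animal naming". Counting each named test or subtest pair once gives ten main measures: COBRA, SCWT, CVFT, C-AVLT, TMT-B, DSFB, DSC, TMT-A, VRP and VRC.

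Section 2.12 (Scale assessments) then says how each score is to be read:

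- **SCWT, CVFT and TMT-B**, in a single sentence: "will be used to assess executive function, with higher scores indicating worse cognitive functioning".
- **COBRA**: "The summed scores of each item yield a total COBRA score, which is negatively correlated with subjective cognitive impairments".
- **C-AVLT**: "The higher number of word recall is associated with better verbal memory".
- **Attention and processing speed**: "Higher scores for TMT‐A represent worse cognitive performance, and higher scores for DSFB and DSC of WAIS‐RS indicate better cognitive functioning".

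The Background section states which way the result is expected to go: "we expect that systemic antidepressant treatments in early stage could negatively affect the neurocognitive function". Section 2.19 (Statistical analysis) compares each scale between the groups by analysis of covariance, then pools the groups and fits multiple linear regressions for neurocognitive function.

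**The concern.** A rule under which higher is worse fits a completion time. It does not fit a test in which the patient names animals and the words are counted. Nor does a total that falls as impairment rises fit an instrument named for the complaints it collects.

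Both measures are main endpoints, and COBRA is the only subjective one. The study asks whether early antidepressant treatment harms cognition, so the sign of each group difference is the answer. If the analyst or the reader takes section 2.12 at its word, fewer animals named in the AT group becomes evidence of better executive function. If COBRA is also reversed, more complaints becomes evidence of less subjective impairment. Each would count against the study's stated expectation when it in fact supports it, or the reverse.

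**Working it through.** There is no figure in the plan to reproduce. The check sets the stated directions beside what the article says each test measures, and then asks what a wrong direction does to the planned analyses.

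**1. CVFT**

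- Measured (2.7): animal naming.
- Natural score: number of animals named, so higher is better.
- Stated direction (2.12): higher is worse.
- Stated reversal or transformation that would reconcile the two: none.
- Comparison within 2.12: C-AVLT, also a count of words, is read as higher is better.

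The stated direction conflicts with the task. This is not a general convention of the article. In the attention domain it separates TMT-A (higher is worse) from DSFB and DSC (higher is better). In the executive domain one direction was applied to all three tests.

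**2. COBRA**

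- Measured (2.7): by its name, cognitive complaints.
- Score (2.12): items are summed.
- Direction expected from the name: a higher total means more complaints, hence more subjective impairment.
- Stated direction (2.12): a higher total goes with less impairment.
- Item anchors or range: not given.

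The two statements pull apart, but without the item scoring the reversal is probable and not proven.

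**3. Effect on the planned analyses**

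For a group comparison, t = (mean in AT − mean in NT) / SE. Replacing every score x by −x changes the sign of the numerator and leaves SE as it was, so t becomes −t and the two-sided p-value does not move. As an illustration only, two groups of 62 were simulated with assumed means of 18 and 20.5 and an SD of 5:

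| Scores | t (122 df) | two-sided p |
|---|---|---|
| as generated | −2.84 | 0.0052 |
| sign reversed | +2.84 | 0.0052 |

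The same holds for an adjusted group difference in the analysis of covariance and for a coefficient in the regression: the magnitude and p-value stay and the meaning of the sign turns over. The p-value therefore gives no warning that the direction was misread.

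**4. Extent**

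Clearly affected: 1 of 10 main measures (CVFT). Probably affected: 1 more (COBRA). Nothing in the article shows the directions stated for the remaining eight to be wrong.

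**The case against.** The strongest reply is that section 2.12 only describes how to read scores and prescribes no coding. The planned tests are two-sided, so no p-value, absolute effect size or sample size depends on the sentence, and if raw animal counts are reported a reader could see the direction for himself. This is right, and it limits the harm to interpretation. It does not remove it: the article states a directional expectation, and the affirmative statement about CVFT is wrong for the test it names. It is not a detail left for an analysis plan to supply. A plan that copied the statement would inherit the error, and one that corrected it would contradict the protocol.

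A second reply is that the COBRA form is not shown and might be scored so that a high total is favourable. That stands, and it is why COBRA is a point to verify.

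Three stronger readings are tempting, and the article does not support them:

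- A reader might infer that a reversed CVFT would dilute an executive or global composite and cost power. Section 2.19 compares scale by scale, and no composite is defined. The composite index mentioned in the Background and Discussion belongs to a cited study.
- A reader might infer that the SCWT direction is wrong too. A direction is stated, and it is correct if time or errors are scored. Which Stroop score is analysed is detail that an article may leave to the full protocol.
- A reader might infer that every test has to be recoded to a common direction. With separate analyses of each scale, correct labels are enough.

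**Conclusion.** The point holds for CVFT with high confidence: the stated direction is the opposite of what animal naming yields. This assumes that the score is the number of animals named. The article does not say so outright, but nothing in it suggests another score, such as an error count. For COBRA the reversal is probable, resting on the instrument's name and the summing of its items, and needs the scoring form to settle it.

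The size is a reversed conclusion on one main measure of ten, and probably on a second, in both the group comparison and the regression. It would be an overreading to say that the main-endpoint results as a whole would carry the wrong sign. The statistical tests and the other main measures are untouched. It should nevertheless be corrected before any result is interpreted, because it bears on the study's central question and the output itself will not reveal it.

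**What to change.** In section 2.12:

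1. Take CVFT out of the sentence it shares with SCWT and TMT-B, and state separately that its score is the number of animals named and that a higher number is better.
2. Check the COBRA direction against the scoring form in use. If the form confirms it, restate that a higher total means more complaints and so worse subjective cognition. If it does not, say how the items are scored so that the stated direction makes sense.
3. Interpret the signs of the group differences and regression coefficients for these two endpoints accordingly.

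The cost is a text correction and one look at a form. No change to the data, the tests or the sample size is needed.
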